**Fig. 1 Fig1:**
[figure not shown]
Audit Project Odense cycle in the HAPPY PATIENT project

### Setting and population

We will carry out the audit registrations and monitor the intervention outcomes in five countries (Greece, France, Spain, Poland, and Lithuania) with diverse antibiotic prescription rates. In each country, data will be collected in four different settings: (a) general practice, including GPs and nurses; (b) secondary care, in out-of-hours (OOH) services, including doctors and nurses; (c) tertiary care, with nursing homes, involving doctors and nurses who directly engage patients in relation to the prescribing and use of antibiotics; and (d) community pharmacies, with pharmacists and pharmacy technicians.

### Project phases

Phase 1 - Codesign study: June–November 2021Phase 2 - Pilot test of the audit registration charts: November 2021Phase 3 - First audit registration: February 2022Phase 4 - Multifaceted intervention: October–December 2022Phase 5 - Second audit registration: February 2023Phase 6 - Results: November 2023

### Phase 1: co-design process

The project co-design process, using a modified Delphi technique, was used to incorporate the opinion of different HCPs in the development of the educational material that will help facilitate the communication between HCPs and patients when discussing the need and use of antibiotics for common CAIs [16, 17]. HCP “experts” from the four different sectors in the HAPPY PATIENT project across the five target countries were contacted by local coordinators and constitute the panel of “experts” that will prioritize areas of improvement.

The expert panel process includes the following steps: (a) review of scientific literature and publicly available surveys at European and national level regarding knowledge gaps associated with inappropriate use of antibiotics in CAIs; (b) first draft of a list of themes based on a literature review; (c) first prioritization round, during which the identified panel of “experts” receive a list of statements and knowledge gaps covering the following domains: knowledge gaps and misconceptions about antimicrobial resistance, use of antibiotics in general, and use of antibiotics for CAIs, namely RTIs and UTIs, and rate each statement on a seven-point Likert scale; (d) individualized feedback; the experts are given individualized feedback in the form of bar charts showing the distribution of ratings from the first round, with the experts’ rating highlighted in the figure and distributed by sector, so differences across countries within the same sector can be discussed; (e) consensus meetings – the panel of experts participate in a discussion about which of the knowledge gaps and misconceptions included in the Delphi study lead to increased inappropriate use of antibiotics in each sector; (f) second assessment of themes, with those reaching > 80% consensus are summarized in the different types of communication and intervention material; (g) iterative modification, during which the panel of experts and identified patient associations receive the first draft of the communication material and participate in a process of discussion, rephrasing and iterative evaluation of the material, resulting in the final version of the communication material. Lastly, on the basis of the NPT framework that uses collective participation and reflection to ensure the success of the intervention and to lead to change in the dimension of changing practice behaviour of the HCPs, the result of the co-design process will be used for the training, audit and workshops that will be conducted during the multifaceted intervention and the APO cycles [17].

### Phase 2: audit registrations

The project will conduct two audit registrations: the first will begin before the intervention (February 2022) and the second will take place after the intervention (February 2023). The same month has been chosen for the implementation of both registrations to minimize the effect of potential seasonal variation in CAIs. A registration pilot testing, in November 2021 with approximately five HCP participants per setting and per country, ensured that the content of the registration chart was relevant to their practice and easily understood, and confirmed that sufficient patients could be recruited.

During the audit period the participants will use the APO registration chart to record all consultations or dispensations regarding the CAIs selected for audit. Participants will be asked to fill in the chart with the consecutive consultations they receive regarding the CAIs selected, and in the case of pharmacies, all the systemic antibiotic dispensations given for acute infections. A specific registration chart for each of the 4 settings has been developed considering their characteristics and the quality improvement areas that HAPPY PATIENT seeks in each setting. The example of the template used in nursing homes is depicted in Fig. 2. At most, 10 main domains and a maximum of 45 variables are used to describe the topic investigated. The main domains are lined up in a logical way; for example: type of contact, symptoms present, examinations performed, diagnosis, treatment, and assessment. According to the APO methodology the variables are exhaustive (include all possibilities) and exclusive (no overlapping), and all follow the same logic plan. One line is filled in for each registered case and, as a general rule, only multiple choice is allowed (no open-ended text). At least one choice per main group is needed. A short instruction sheet will be provided for all HCP participants, with details about the registration period, the inclusion and exclusion criteria for the cases and a brief explanation of the content of each main group.

**Fig. 2 Fig2:**
[figure not shown]
Draft of the template to be used in nursing homes in the HAPPY PATIENT project (patients receiving antibiotics).

Data originating from the registration will be used for quality assessment using quality indicators. In the case of general practice, OOH services and nursing homes, an indicator of antibiotic inappropriateness is considered. Antibiotic prescribing is considered appropriate if it fulfils the following criteria: a) the diagnosis for which this is given might be bacterial; b) it is suspected that the criteria presented by the patient are caused by bacteria; and c) the choice of the antibiotic reflects the local pathogens and resistance patterns in each setting. Anything else is inappropriate. Although antibiotic underprescribing – withholding antibiotic use when the infection is suspected to be of bacterial origin – is also inappropriate, this is negligible in western countries according to the medical literature [18]. Based on the charts used in the registrations the group defined when an antibiotic was appropriate or not. In the case of pharmacies, several indicators have been defined, based on the safety and the appropriate advice given to the patients. Figure 3 describes the example used in OOH services.

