### Statistical analysis plan

Statistical methods for inference in small samples will be used according to a statistical analysis plan. The minimum number of HCPs per APO audit cycle has been estimated based on the assumption that each HCP will register about 25 cases, including either consultations or dispensations, during the audit registration. A decrease of 15% in antibiotic prescribing can be expected after the intervention (from about 40% before to about 25% after). The within-practice correlation coefficient is 0.1. If the comparison is to be performed at the 5% level of significance (two-sided) with 80% power, then the number of HCPs to be included should be 25 per APO cycle. There will be 20 APO cycles in the project (one for each of the 4 healthcare settings involved in each of the 5 target countries). We assume the participation of 500 HCPs in the project and the registration of 25,000 cases.

We will apply the Fisher exact test to the frequencies of prescriptions before and dispensations before and after the audit for each group of professionals and setting/country to test the null hypothesis of no effect of the audit. We will also estimate the effect of the interventions with logistic two-level regression models: a) cases of CAIs and b) HCP participants. Antibiotic prescription will be considered as the dependent variable (yes/no) as well as the concepts of inappropriate prescribing and inappropriate dispensing. These models control for symptoms and duration, as well as for the demand for antibiotics by the patient. Goodness of fit will be assessed using the Wald test of the model, with the deviance test to compare alternative models. Statistical significance will be considered with *P* < 0.05. The data will be analysed using Stata v16.

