## Discussion

AMR is a growing problem that threatens social development, human and global health. Infections caused by antibiotic-resistant bacteria are associated with a greater need for medical visits, more hospital admissions, higher mortality, and higher economic costs. Reducing the unnecessary prescription of antibiotics has been shown to be the most effective measure to curb the problem of AMR. Despite the high use of antibiotics and the growing development of AMR, only a few initiatives have been carried out to reduce the inappropriate use of antibiotics in more than one setting. The aim of the HAPPY PATIENT study is to evaluate the impact of a multifaceted intervention programme focusing on appropriate treatment of CAIs and targeting different types of HCP who constitute the first contact with the patients (doctors, nurses, pharmacists) and patients in the community. To our knowledge no other study has taken all these sectors into account. In addition, the study takes place in five European countries with diverse prevalence of antibiotic resistance, and with different cultural backgrounds and different healthcare organisations, increasing the extrapolation of the findings to a wide range of settings. The intervention will combine several techniques, including feedback to HCPs, training courses, follow-up meetings, discussion of guidelines, enhancement of communication skills, posters for waiting rooms and leaflets to the patients. We anticipate that inappropriate antibiotic prescribing and dispensing will be lowered after the intervention in the four settings, as has been shown in other studies with the use of the same APO methodology [12, 13].

The APO cycles in this study will be performed in a real-life practice setting and patients will not be informed about the project prior to the consultations or dispensations. HCPs participating in the audit will not be allocated extra time for consultations or dispensations, and they will not be able to make considerable changes in their practice activities during the registration. Thus, they will see the patients in the same way they would if not participating in the audit.

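### The article contradicts itself on whether untreated nursing-home patients are registered, and on one reading the prescribing outcome and its sizing do not apply to the five nursing-home cycles

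*Protocol article*

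**What the plan says.** Three places in the protocol article bear on who is registered in nursing homes.

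- **Phase 2: audit registrations, running text.** Participants are to "record all consultations or dispensations regarding the CAIs selected for audit". The one stated restriction to antibiotic cases is "in the case of pharmacies, all the systemic antibiotic dispensations given for acute infections". The same section says "A specific registration chart for each of the 4 settings has been developed" and "The example of the template used in nursing homes is depicted in Fig. 2".
- **Caption of Fig. 2.** "Draft of the template to be used in nursing homes in the HAPPY PATIENT project (patients receiving antibiotics". No second nursing-home chart for untreated patients is mentioned.
- **Statistical analysis plan section.** "Antibiotic prescription will be considered as the dependent variable (yes/no) as well as the concepts of inappropriate prescribing and inappropriate dispensing". The sample size rests on prescribing falling from about 40% to about 25%, and the resulting number of professionals is applied to each of 20 cycles (4 settings in 5 countries). No setting is excepted.

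On the quality outcome, the text below Fig. 2 states: "In the case of general practice, OOH services and nursing homes, an indicator of antibiotic inappropriateness is considered". It gives no denominator for that indicator. The Discussion predicts: "We anticipate that inappropriate antibiotic prescribing and dispensing will be lowered after the intervention in the four settings".

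**The concern.** A yes/no prescribing outcome needs untreated cases in the data, and so does a fall from 40% to 25%. A chart for patients receiving antibiotics has none. For nursing homes, the caption and the other two passages cannot all be right.

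If the caption is right, there are two consequences. The prescribing outcome is constant and cannot be analysed in 5 of the 20 cycles, so the stated power does not cover them. The only prescribing outcome left there is inappropriateness among treated patients. Being treated is what the intervention is meant to change, so the second audit would then compare a differently selected group with the first. The predicted fall in inappropriate prescribing could be understated or hidden in that setting.

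This cannot be left to later analysis: patients who were never registered cannot be recovered from the data.

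**Working it through.** **1. The plan's own figure.** Inputs from the Statistical analysis plan section: 40% before, 25% after, correlation 0.1, 25 cases per professional, two-sided 5%, 80% power.

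- Cases per audit without clustering: n = [1.96·√(2·0.325·0.675) + 0.842·√(0.40·0.60 + 0.25·0.75)]² / 0.15² ≈ 152, or 165 with continuity correction.
- Design effect: 1 + (25 − 1)·0.1 = 3.4.
- Professionals: 152·3.4/25 = 20.7, so 21; with correction, 165·3.4/25 = 22.4, so 23.

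The stated 25 is close to the corrected figure. With 25 professionals the effective sample is 625/3.4 ≈ 184 per audit, and power is about 87%. The sizing is sound for the outcome it assumes. That outcome is the share of all registered infections that are treated.

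**2. The same figure on a treated-only chart.** Every line is a treated patient, so prescribing is 100% before and 100% after. There is no 40%, no 25% and nothing to test. This affects 1 setting × 5 countries = 5 of 20 cycles.

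**3. What the inappropriateness share then measures.** For a given number of infections, let I be inappropriate courses, T all courses and S = I/T. Then

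S₁/S₀ = (I₁/I₀) ÷ (T₁/T₀).

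With the plan's fall, T₁/T₀ = 25/40 = 0.625, so S₁/S₀ = 1.6 × (I₁/I₀) at any baseline share. Whenever total courses fall, the share shows a smaller relative fall than the inappropriate courses themselves (unless these vanish altogether).

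**4. Illustration per 100 infections.** Treated patients fall from 40 to 25 (the plan's figures), so 15 courses are avoided. The article gives no baseline inappropriate share; 50% is assumed, which is 20 of 40. If a fraction f of the avoided courses was inappropriate, the second-audit share is (20 − 15f)/25.

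| f | Inappropriate courses | Appropriate courses | Share among treated |
|---|---|---|---|
| 1/4 | 20 → 16.25 (−18.75%) | 20 → 8.75 (−56.25%) | 50% → 65% |
| 1/2 | 20 → 12.5 (−37.5%) | 20 → 12.5 (−37.5%) | 50% → 50% |
| 3/4 | 20 → 8.75 (−56.25%) | 20 → 16.25 (−18.75%) | 50% → 35% |
| 1 | 20 → 5 (−75%) | 20 → 20 (0%) | 50% → 20% |

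With all infections as the denominator, each row shows a fall: from 20% to 16.25%, 12.5%, 8.75% and 5%.

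**5. Range for the assumed baseline.** At baseline shares of 20%, 40% and 60%, an equal proportional fall takes inappropriate courses from 8 to 5, 16 to 10 and 24 to 15. Each is a fall of 37.5%, and the share stays at 20%, 40% and 60%.

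**The case against.** The treated-only reading rests on one parenthesis in the caption of a template called a draft, and only the caption, not the image, could be read here. The parenthesis might label one part of the chart. The inclusion criteria are in an instruction sheet and further detail in a separate analysis plan, neither of which is shown. The running text points to registering all infections. This stands: a reader might infer that nursing homes certainly register only treated patients, and the article does not settle that. It does not remove the contradiction, because one specific chart per setting together with that caption makes treated-only the likelier description of the chart, against the other two passages.

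A reader might also infer that the nursing-home outcome is unable to show a benefit. The article does not support that. In the last two rows of the table the share falls to 35% and 20%. A flat or rising share needs appropriate courses to fall by at least the same proportion as inappropriate ones. The intervention teaches guideline-based use (Table 3), and the article regards underprescribing as negligible, so this is possible but not what the plan expects.

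Finally, a reader might infer that the nursing-home indicator measures something different from the same indicator in general practice and out-of-hours services. No denominator is stated for any of the three, so this cannot be shown.

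**Conclusion.** The point holds as a contradiction with conditional consequences. The Fig. 2 caption cannot be reconciled with the all-consultations rule and with a prescribing outcome sized on 40% to 25% in every cycle. If the chart is treated-only, that outcome and that sizing drop out for five of 20 cycles.

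The inappropriateness share would then understate any fall in inappropriate courses whenever total courses fall, by a factor of 1.6 on the ratio if courses fall as planned. It would be flat or rise only if appropriate courses fell at least in proportion. The factor of 1.6 uses the plan's own figures and a fixed number of infections, and does not depend on the baseline share; the shares in the table rest on the assumed 50%. If all infections are registered, the error is confined to the caption and the unstated denominator. Either way it should be settled, because it decides what can be concluded for nursing homes.

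**What to change.** Reconcile the registration rule, the Fig. 2 caption and the statistical section, and state the indicator's denominator.

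- **If all infections are registered:** correct the caption and use all registered infections as the denominator of the inappropriateness indicator. The cost is a change of text.
- **If only treated patients are registered:** take the five nursing-home cycles out of the yes/no prescribing outcome and out of the 40% to 25% power statement. Report the share as quality among treated residents, and state that a change in share alone will not be read as less or more inappropriate prescribing. The cost is a narrower claim for nursing homes than the Discussion now makes.

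In the second case, add a supporting analysis: total and inappropriate courses per professional per audit, shown together, with registration days as exposure. This costs one further model per nursing-home cycle and one extra field, since the article does not say that registration days are recorded. It should not become the main estimate. The counts also move with infection incidence and completeness of registration between the two Februaries, and with the target of about 25 cases per professional: if participants stop near that number, only the duration carries information.

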**Fig. 3 Fig3:**
[figure not shown]
Defining antibiotic appropriateness in out of hours services in the HAPPY PATIENT project

### Phase 3: multifaceted intervention

In each of the five target countries, face-to-face or online training workshops plus a few online courses will be given to each of the four groups of HCPs. These will take place approximately 3 months before the second registration (October–December 2022) and will be run by the local coordinators of the project. In these workshops, the HCPs will discuss the results of the first audit and set goals for antibiotic prescribing or dispensing based on the audit results, expert involvement, and the EU AMR Guidelines. The elements of this multifaceted intervention are described in the Table 3.

**Table 3 Tab3:** Components of the multifaceted intervention

• Provision of individual prescriber or dispenser feedback of the results of the first registration at an individual and group level, identifying potential quality problems from the first registration reflecting the quality of their own care provided and giving peer-to-peer feedback.	
• Training course on the appropriate use of antibiotics for common CAIs, with clinical guidelines on recommendations for the diagnosis and treatment of infections.	
• Enhancement of communication skills to be used during the consultation or dispensation with patients with CAIs.	
• Training material on evidence-based management of CAIs with an explanation of the natural course, management, and safety netting.	
• Posters for waiting rooms focused on the appropriate use of antibiotics.	
• Educational material on the rational use of antibiotics for patients, such as brochures and handouts about prudent use of antibiotics and an explanation of the concept of the antibiotic footprint. This material will be accessible at the point of contact and during the encounter with the HCP.	

The proposed multifaceted intervention seeks to address all the dimensions of the NPT by facilitating open discussion on the variation in practice behaviour and strengthening the communication between the HCPs and the patients. Strengthening communication is a key element of our patient-centred approach. Several studies have shown that most patients do not necessarily want an antibiotic prescription but want time to talk to the HCP about their concerns [19]. Communication skills training includes strategies to address patient concerns regarding diagnosis, prognosis, benefits, harms of antibiotic treatment, how to manage patient expectations for antibiotics and provide alternatives during a clinical encounter. Therefore, communication training, providing HCPs with succinct and understandable arguments to communicate with their patients, and explanation guidelines is anticipated to decrease antibiotic use [20]. Reports comparing the results of the two audits and showing the progress on meeting the quality indicator goals will be produced, while participants will meet for a second round of peer-to-peer feedback and further goal setting.

### Limitations of the study

The use of the APO method has some limitations. Perhaps the most important limitation of the data collected is the lack of external validity. HCPs participate on a voluntary basis and their prescribing or dispensing habits might not represent the average use of antibiotics in their country. Additionally, HCP providers participating in audits may be more interested in quality development and might have a more rational use of antibiotics than non-participating HCPs [21]. Another limitation which should be considered is the fact that performing an audit may itself influence providers’ prescribing or dispensing behaviours when HCPs know they are being observed, leading to the, so-called, Hawthorne effect.

The amount of time needed to be involved in a quality improvement project could be a relevant barrier to participation. However, while filling out one registration takes less than 2 min, HCPs need to set aside time for the educational courses or other activities planned in the intervention. The APO methodology has been widely used in general practice, but not as much in OOH services and nursing homes as to our knowledge, this is the first time it will be used in community pharmacies. The cross-sectional nature of the APO method is another weakness. Variables included in the registration chart are lined up in a certain way to align with the consultation or dispensation process. Theoretically, the decision to treat should be taken after a diagnosis has been established. In general practice, however, the diagnostic procedures and the decision to treat are intertwined [22]. HCPs may decide whether to prescribe a drug at the same time, or even before. After making the decision to prescribe, clinicians may thus adjust the diagnosis to fit the decision about treatment. This may lead to a diagnostic misclassification bias. However, this potential bias will affect the validity of the diagnosis both before and after the intervention and the likelihood of influencing the effect of the intervention is small.

Due to the limited time allocated for the registration process, only the typical signs and symptoms for RTIs and UTIs will be collected. This may lead to some limitations. Non-biomedical factors that may represent powerful predictors of antibiotic prescription are not considered in this study. This limits the definition used for antibiotic appropriateness in our study as this is based on the different items collected in the registration charts. Another limitation is the lack of studies using the APO method in the pharmacy setting. In addition, the use of over-the-counter antibiotics, still available in some European countries, is not covered in this study.

